### Secondary outcome measures

The secondary outcome measures will include the participant’s performance in all cognitive assessments, performance in pattern separation task, hippocampal microstructure (as measured on 3T MRI) and seizure frequency. Learning and memory outcomes will be assessed across spatial, visual and verbal domains. The spatial domain will be assessed using the distance travelled and latency to find the hidden platform in the virtual water maze. Performance during probe trials will be measured using the proportion of time participants spend searching in the four quadrants of the pool and the platform area, the latency and distance travelled to cross the platform area, and the number of times the platform area was crossed. The visual domain will be assessed by using the recall accuracy of images recorded using the SenseCam wearable camera (scores), and the verbal domain will be assessed using word list learning and delayed recall scores.

For the pattern separation task, performance will be determined by the ratio of correct to incorrect responses and response latencies. Measures of hippocampal microstructure will be derived from diffusion-weighted MRI acquired before and after trial treatment. Seizure frequency will be determined from the analysis of events recorded in participant’s seizure diaries.

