
For the pattern separation task, participants enter a computer-generated arena facing a particular direction and are then presented with a visual stimulus located in one of 20 pre-determined spatial locations within the arena. The participant must then navigate to the stimulus using the arrow keys on a keyboard, and once at the stimulus, they must press the space bar to initiate the next part of the trial. For the choice phase, the participant is presented with four visual stimuli in a square formation; one corner is in the same spatial location as the previous stimulus and the other three stimuli are foils. The participant must navigate to the stimulus presented in the location of the original stimulus using extra-arena cues and press the space bar to indicate their choice within the 45 s time limit of the trial. Across trials, three separation distances between the grouped stimuli will be used (minimum, intermediate and maximum) in a pseudorandom order. Twenty-one test pairs (seven per condition) will be presented in total.

In the SenseCam task, participants will be asked to attend a local tourist attraction, accompanied by a family member or friend, who has given their consent to participate, whilst wearing a SenseCam camera which hangs around the neck at chest level. Following the excursion, the researcher will extract 4–5 snapshot images of six events in order to test the participant’s recall of the excursion. The person accompanying the participant will be presented with the same images and asked to recall details of the excursion in the same manner to provide control responses to those of the participant. Images will be presented on a laptop screen and participant will be given as long as they like to look at the image. They will be asked to recall the event pictured and secondary details associated with it—the events occurring either immediately before or after the presented event. Each correct recollection is given a one-point score giving a maximum possible score of 3 per picture presented. Participants will be tested on their recall on day 1, day 2 and day 21 of each testing block.

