### Analysis

As this is a feasibility trial, no formal hypothesis testing will be conducted. The components of the primary outcome (recruitment, retention, adherence) will be presented as numbers and/or percentages, as appropriate, and assessed against pre-specified progression criteria (Table 2). All secondary outcomes will be summarised descriptively, by treatment arm. Categorical data will be summarised by number and percentage. Continuous data will be summarised by mean and standard deviation, or median and interquartile range if notably skewed. For each outcome, the relevant complete case population will be used, and participants will be analysed as randomised (intention-to-treat). Details of the analysis are specified in the trial statistical analysis plan.

For the qualitative interviews, transcribed interviews will undergo manual analysis to identify themes within the data using NVivo software. Identified themes will be used to categorise and summarise participant responses. A proportion of interviews (10%) will be randomly selected for double coding to ensure all relevant data is captured.

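### The pattern separation score, correct answers divided by incorrect ones, is undefined for an error-free participant and unstable near ceiling; proportion correct avoids both

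*Protocol article*

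**What the plan says.** In Secondary outcome measures, the article fixes the scoring of the pattern separation task: "performance will be determined by the ratio of correct to incorrect responses and response latencies". It does not say whether the ratio is formed within each separation or over the whole task.

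The task is described under Trial assessments. In the choice phase "the participant is presented with four visual stimuli in a square formation", one of them in the right place and three foils, with 45 s to choose. Across trials "three separation distances between the grouped stimuli will be used (minimum, intermediate and maximum) in a pseudorandom order". The amount of data is also given: "Twenty-one test pairs (seven per condition) will be presented in total".

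Under Analysis, outcomes are described by arm without hypothesis tests: "Continuous data will be summarised by mean and standard deviation, or median and interquartile range if notably skewed". On the population it says "For each outcome, the relevant complete case population will be used", and it refers further detail to the statistical analysis plan, which is not shown. The Backgrounds section and the Discussion both say the trial is meant to supply effect sizes for a later efficacy trial.

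**The concern.** A ratio with the number of errors as denominator has no value for a participant who makes none. It also treats equal gains in performance very unequally: one further correct answer barely moves a middling score but can double a good one. The default summary in the Analysis section is a mean and SD, and both are sensitive to a few extreme values.

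What is at stake is the usefulness of this outcome for planning. A phase II sample size needs a usable mean difference and SD. With about 10 participants per arm, one participant near ceiling could set both figures, and one at ceiling would leave them incalculable unless a special rule is added. The score also serves the secondary objective on whether a pattern separation deficit predicts response to fluoxetine. The article itself says, under Trial assessments, that floor and ceiling effects are of interest, and the ceiling is where this score fails.

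**Working it through.** **Inputs from the article.** 21 test pairs, 7 per separation, 4 response options (Trial assessments); planned sample of 20 (Recruitment and consent) allocated 1:1 (Randomisation, allocation concealment and blinding), so about 10 per arm. The article has no figure for this outcome to reproduce. Its one precision figure, ±22 percentage points for feasibility rates, does reproduce (1.96 × √(0.25/20) = 0.219) but has no bearing here.

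**Assumptions.** The article gives no expected accuracy, so *p*, the probability of a correct answer, is ranged. Trials are taken as independent, with the same *p* for everyone.

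**Step 1: shape of the score.** With *k* correct out of *n* and every other trial an error, the score is *k*/(*n* − *k*), undefined at *k* = *n*.

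| Correct/incorrect, 21 pairs | Score | Correct/incorrect, 7 pairs | Score |
|---|---|---|---|
| 18/3 | 6.0 | 4/3 | 1.33 |
| 19/2 | 9.5 | 5/2 | 2.5 |
| 20/1 | 20.0 | 6/1 | 6.0 |
| 21/0 | undefined | 7/0 | undefined |

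Mid-scale, one more correct answer moves the score from 10/11 = 0.91 to 11/10 = 1.10, a step of 0.19. Near the top, 19/2 to 20/1 is a step of 10.5, about 55 times as large. In an arm of 10, that single answer moves the arm mean by 10.5/10 = 1.05. On proportion correct, the same answer moves the participant's score by 1/21 = 0.048 wherever it falls on the scale.

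**Step 2: how often the score is undefined.** P(no errors) = *p*^*n*; the expected number per arm is 10 × *p*^*n*.

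| Assumed *p* | P(no errors), 7 pairs | Per arm of 10 | P(no errors), 21 pairs | Per arm of 10 |
|---|---|---|---|---|
| 0.50 | 0.8% | 0.08 | <0.01% | 0.00 |
| 0.70 | 8.2% | 0.8 | 0.06% | 0.006 |
| 0.80 | 21.0% | 2.1 | 0.9% | 0.09 |
| 0.90 | 47.8% | 4.8 | 10.9% | 1.1 |

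The scoring unit matters as much as accuracy. Per separation, undefined scores are likely once accuracy reaches about 0.80. Over the whole task they are rare at 0.80 and become noticeable at 0.90.

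**Step 3: what would follow if undefined scores were dropped.** This is conditional, because the article states no such rule. Among participants with at least one error, mean accuracy on 7 pairs would be 0.747 where the true value is 0.80, and 0.808 where it is 0.90. On 21 pairs it would be 0.798 and 0.888. Suppose the two arms had those two accuracies, a true difference of 0.10. The observed difference would be 0.808 − 0.747 = 0.061 on 7 pairs and 0.888 − 0.798 = 0.090 on 21.

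The ratio itself does not behave so simply. The true odds are 0.8/0.2 = 4 and 0.9/0.1 = 9, a difference of 5. After dropping, the mean ratios are 3.88 and 4.94 on 7 pairs (difference 1.06), but 5.32 and 10.75 on 21 pairs (difference 5.43). The distortion can go either way.

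**Step 4: the alternative.** Proportion correct, *k*/7 or *k*/21, is defined for every count. An error-free participant scores 1.00, and chance is 1/4 = 25%.

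**The case against.** The strongest reply is that the harm is inferred. A reader might conclude that the complete-case rule removes the best performers. The article does not say so: someone with seven correct and no errors has fully observed data, nothing states that an undefined ratio counts as missing, and a zero-error rule may be in the analysis plan. That stands. So does its corollary: a reader might infer bias towards no difference between arms, but this needs the unstated dropping rule, and Step 3 shows that the direction is not fixed even then.

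The frequency is also uncertain. The accuracy range has no source in the article; these are patients with hippocampal sclerosis facing a four-choice task, and whether they have a deficit is one of the study questions. At accuracy 0.50, or with scoring over all 21 pairs, error-free results are rare. This limits the size of the problem but leaves the defect in the score.

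The article also allows median and interquartile range for skewed data, and an error-free score can be ranked highest. This helps in part. The median survives while fewer than half of an arm are error-free, but the upper quartile is lost once about a quarter are, and no SD or standardised effect size follows from ranks. Response latencies do remain available for error-free participants.

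Finally, a reader might extend the point to the water-maze probe, where "the latency and distance travelled to cross the platform area, and the number of times the platform area was crossed" are measured and a participant who never crosses has no latency. The documents do not support a finding there. Movements are traced for a fixed 45 s, treatment of non-crossers is commonly left to the analysis plan, and the number of crossings and time in each quadrant, both planned outcomes, are defined for non-crossers.

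What survives is that the ratio is a metric the article states, not a detail it leaves out. An analysis plan would have to patch or replace it.

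**Conclusion.** The point holds as a weakness in a stated metric. That the ratio is undefined at zero errors and jumps from 9.5 to 20 on one answer is plain arithmetic on the article's own trial counts and needs no assumption about accuracy or missing data. How many participants would be affected cannot be settled from the article: at assumed accuracies of 0.70 to 0.90 it is 0.8 to 4.8 per arm of 10 in a given separation, but only 0.006 to 1.1 per arm over the whole task, with independent trials and equal accuracy across participants.

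The consequence is confined to the descriptive summaries of this outcome and to any effect size taken from it for the next trial. The secondary objectives are described as largely exploratory, no test is planned, and no progression criterion in Table 2 uses the score, so the feasibility conclusion is untouched. It is a worthwhile improvement at no cost, not a threat to the trial.

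**What to change.** In Secondary outcome measures, replace the ratio with the proportion of correct responses, reported out of 7 for each separation and out of 21 overall, with the 25% chance level shown for reference. State that a trial with no choice within the 45 s limit counts as not correct, so that the denominator is always the number of pairs presented. Response latency can stay as the second measure.

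The change is one of wording. The same responses are used, no further data are collected, and the sample size is unaffected. If the analysis plan or database repeats the ratio definition, it should be brought into line before arm-level results are seen.

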### Qualitative interviews

To gain a better understanding of factors influencing the participation of people with TLE in a trial such as this, we will be conducting semi-structured interviews with a variety of stakeholders. Interviews will be conducted with full written informed consent with (1) participants who agreed to take part in the trial, including those who were deemed to be ineligible; (2) participants who were invited to take part and declined; and (3) clinicians involved in the identification and recruitment of participants. We will aim to interview 15–20 people who have given written, informed consent to gain a wide range of views and opinions. Interviews will be conducted in a place of the participant’s choosing, which could include telephone interviews. Interviews will be audio recorded and transcribed verbatim for analysis.

### Data management and monitoring

All participants recruited to the trial will receive a unique participant identification number (PID) which will be used to anonymously identify all files and study materials relating to them. Personal identifiable data required for scheduling assessments will be stored in a password-protected database, separate from the main trial database on a securely networked computer and accessible only to the trial manager and CI.

For all standard cognitive assessments and validated rating scales, data will be collected in the appropriate published booklet and data entered into the on-line trial database. Questionnaire data will be collected via electronic case report forms (CRFs) allowing direct entry into the database. The computer-based cognitive assessment will automatically collect the required data, and the summary variables required for each test will be entered into the trial database. For all assessments, paper CRFs are available for recording data for circumstances where the trial database may be off-line. The trial database is held on securely networked servers with automatic backup. It is tested and validated with in-built range checks to ensure the accuracy and validity of data at the point of entry. All procedures for handling and storing both electronic and paper records are detailed in the trial data management plan.

Data will be monitored centrally on a routine basis and any queries raised directly with trial researchers. These will be monitored monthly by the trial management group. Trial steering (TSC) and data monitoring committees (DMC), independent of the trial sponsor, will be convened at regular intervals throughout the course of the trial. The DMC will review period safety data (unblinded if requested) and report any concerns to the TSC. If there are concerns that there is a clinically important difference in serious AE rates between study arms, then the TSC can make a decision to terminate the trial early with input from the DMC.

### Analysis

As this is a feasibility trial, no formal hypothesis testing will be conducted. The components of the primary outcome (recruitment, retention, adherence) will be presented as numbers and/or percentages, as appropriate, and assessed against pre-specified progression criteria (Table 2). All secondary outcomes will be summarised descriptively, by treatment arm. Categorical data will be summarised by number and percentage. Continuous data will be summarised by mean and standard deviation, or median and interquartile range if notably skewed. For each outcome, the relevant complete case population will be used, and participants will be analysed as randomised (intention-to-treat). Details of the analysis are specified in the trial statistical analysis plan.

For the qualitative interviews, transcribed interviews will undergo manual analysis to identify themes within the data using NVivo software. Identified themes will be used to categorise and summarise participant responses. A proportion of interviews (10%) will be randomly selected for double coding to ensure all relevant data is captured.

## Discussion

This feasibility trial is the first step towards determining the efficacy of fluoxetine as a treatment for the learning and memory problems associated with TLE [6]. The ultimate goal for the study is to see if a larger, fully powered efficacy trial investigating fluoxetine as a therapeutic agent for learning and memory problems in TLE is feasible and warranted.

This trial is designed to gather information on potential effect sizes in novel cognitive assessments translated from work in animal models of TLE and cognition. Further, we will be gathering information on the utility of relatively novel cognitive testing paradigms. Validation of such outcome measures could have wide-reaching implications for the study of cognition and in the investigation of novel therapies to improve learning and memory in epilepsy and other neurological disorders and represents a particular strength of this work. The investigation of fluoxetine in this context may also provide mechanistic insights into human adult cognition and the role of neurogenesis therein, albeit as an indirect measure as changes to human adult neurogenesis cannot be quantified. The purposeful exclusion of participants with active depression or anxiety has been incorporated into the study design to eliminate, as far as possible, the possible confounding effects of depression and anxiety on cognitive performance in the participants studied as depression status and cognitive performance are interlinked [72]. However, due to the high prevalence of depression and anxiety in people with epilepsy [73], this could have profound effects on recruitment rates and overall generalisability of this study, which is a limitation of the work.

The MR images captured as part of this study will be used to investigate whether fluoxetine treatment affects diffusion MRI measures of tissue microstructure in the hippocampus and/or its associated white matter pathways. To the best of our knowledge, this type of analysis has not been reported previously and is highly novel. Whilst this technique cannot directly measure any potential increase in neurogenesis, it will be interesting to see if fluoxetine treatment has any direct effect on hippocampal microstructure. We will also be able to investigate any structure-behaviour correlations between hippocampal microstructure metrics and performance in our cognitive tasks.

The findings of this trial will advance current knowledge in terms of understanding how fluoxetine is tolerated in people with epilepsy. The effect of fluoxetine on seizure frequency is still debated [35–39], so the tracking of seizure frequency in participants of this trial will provide further information for epilepsy clinicians concerned about prescribing fluoxetine to their patients.

A particular strength of this study will be realised through obtaining the views and opinions of participants taking part and perhaps, more importantly, those who chose not to take part in the trial will contribute to the understanding of potential barriers of facilitators underpinning the participation of people with epilepsy in this trial. Further, this information may also contribute to the understanding of why people with epilepsy may or may not take part in research and clinical trials in general, providing valuable information for the future development of research studies involving people with epilepsy.

Participants receiving the intervention in this trial have the potential to benefit from improved learning and memory using a relatively, cheap, widely available and generally well-tolerated medication, which may improve quality of life in people with TLE [8]. This could also have further societal benefits by reducing demand on carers and further enabling people with TLE to have active and productive working lives.

## Trial status

The trial is sponsored by Cardiff University ([contact]) and is currently open to recruitment. This manuscript was drafted according to version 8.0 (December 18, 2018) of the protocol. The protocol was written according to the Standard Protocol Items: Recommendations for Interventional Trials (SPIRIT) statement [74].

## Data Availability

This section is not applicable.

## Abbreviations

AED: Anti-epileptic drug
BMIPB: Brain Injury Rehabilitation Trust Memory and Information Processing Battery
BNF: British National Formulary
CI: Chief investigator
CRF: Case report form
DMC: Data monitoring committee
DT-MRI: Diffusion tensor magnetic resonance imaging
ECG: Electrocardiogram
EEG: Electroencephalogram
EMQ: Everyday memory questionnaire
FA: Fractional anisotropy
MD: Mean diffusivity
HADS: Hospital Anxiety and Depression Scale
HS: Hippocampal sclerosis
IQ: Intelligence quotient
3T MRI: 3 Tesla Magnetic Resonance Imaging
PICs: Participant identification centres
PID: Participant identification number
PIS: Participant information sheet
ROIs: Regions of interest
SPC: Summary of product characteristics
SSRI: Selective serotonin re-uptake inhibitors
TLE: Temporal lobe epilepsy
TOPF: Test of premorbid functioning
TSC: Trial steering committee
QOLIE-31: Quality of Life in Epilepsy-31
WASI: Wechsler Abbreviated Scale of Intelligence
